## 2. OBJECTIVES AND HYPOTHESES

The overall aim of this study is to describe the prevalence and predictors of undiagnosed stage 3 CKD in priority countries.

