### CRDS Database (China)

In December 2018, the National Clinical Research Center for Kidney Disease, the Center for Chronic Non-communicable Disease Prevention and Chinese Center for Disease Control and Prevention jointly established the Chinese Renal Disease Data System (CRDS). By the end of

November 2022, the CRDS database contained 24 Grade 3A hospitals, including 16,953,679 patients with data collected from 1994 to 2022, and consisting mostly of hospital-wide data. Data governance has been completed in 19 hospitals with 15,245,055 patients. The data of rest 5 hospitals has been governed in the CRDS database after 2022 and given the characteristics and of the CRDS database, we will exclude hospitals with data only from nephrology departments; with 20 remaining hospitals that will be included. Observation start date will be January 1 2015 and observation end date will be 31 December 2020 according to quality and situation of CRDS database.

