## 4.3 Other Variables and Covariates

The following baseline variables will be examined. Unless otherwise specified, medical history/comorbidity will be assessed using all available data prior to the index date. Baseline physiological and laboratory values will be extracted at the point of index date or using the most recent values during the 12 months before the index date. Similarly, medication use will be ascertained on or within 12 months before the index date.

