### Sensitivity Analysis

To calculate the robustness of our undiagnosed CKD definition (identified through 2 eGFR measures and no ICD-9/10 CKD diagnosis codes, and OHDSI ICD-10 CN2016 is used in the CRDS database), we will conduct sensitivity analyses 1-2 that assess whether the lack of healthcare encounters, as originally defined, truly captures an undiagnosed population.

Sensitivity analysis for undiagnosed CKD includes ICD-9/10 diagnosis codes for stage 3 CKD or higher

Sensitivity analysis for undiagnosed CKD includes ICD-9/10 diagnosis codes for CKD based on a broader definition derived by Winkelmayr *et al.*, 2005 ([section 8](#)). We will conduct sensitivity analysis 3 to assess if we have included sufficient individuals with undiagnosed CKD in the database, as required by study inclusion [criteria 2](#).

Sensitivity analysis for adjustment of inclusion criteria 2 from “at least 12 months of continuous presence in the database or registration in the data prior to the first qualifying eGFR (for data sources with information on enrollment)” to “at least one medical visit with diagnostic record within  $\leq 12$  months prior to the first qualifying eGFR”. There are no changes in any other inclusion and exclusion criteria. Analyze undiagnosed CKD according to the primary study definitions using eGFR measures captured within a specific time period prior to diagnosis.

- *Time to CKD diagnosis*

For the cohort of patients with no CKD diagnosis code as of the study index date (cohort 2), the median (95% CI) time in days/months from the study index date to physician-diagnosed CKD (using the primary CKD study definition) will be calculated using the Kaplan-Meier method. Survival times will be censored as of the last day of follow-up for patients who remain undiagnosed by a physician. Time to physician diagnosis of CKD will be calculated overall and by patient characteristics and comorbidities. If possible, association between baseline characteristics and time to CKD diagnosis will be assessed using relevant regression models. The time to physician diagnosed stage 3 CKD or higher (sensitivity analysis #1) and the time to CKD using a broader definition (sensitivity analysis #2) ([section 8](#)) will also be calculated.

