### **Secondary objectives**

- *Trends over time*

Trends in the prevalence of undiagnosed CKD over time will be examined by calculating the prevalence during each calendar year of available data. Patients who have a second qualifying

eGFR measurement for stage 3 CKD (index date) during a given calendar year will contribute data toward the calculation of prevalence for that year. It is possible that some patients may contribute data as an undiagnosed stage 3 CKD case during one calendar year, and as a diagnosed stage 3 CKD case during a subsequent calendar year. However, once patients have a physician diagnosis of CKD, they cannot contribute data as an undiagnosed case during subsequent calendar years. It is also possible that some patients may have an initial diagnosis code for CKD that occurs <6 months following their qualifying eGFR, but in a subsequent calendar year. These patients should be classified as “diagnosed” during the year of their qualifying eGFR. In the same way, patients should be classified as “undiagnosed” during the year of their qualifying eGFR if their diagnosis code occurs >6 months following their qualifying eGFR in a subsequent calendar year.

- *Diagnosed versus undiagnosed CKD (baseline characteristics)*

Baseline characteristics will be summarized for diagnosed and undiagnosed CKD patients to compare relevant descriptive statistics and absolute standardized differences. A logistic regression model examining baseline factors associated with undiagnosed CKD will be conducted. The dependent variable is not having CKD diagnosed by a physician as previously described (e.g., presence vs. absence). Baseline characteristics as defined in [section 4.3](#) will be included in the model. Parameter estimates along with odds ratios, 95% C.I.s and p-values will be reported.

The proportions of patients receiving treatment for CKD (ACEi, ARB and SGLT2i) within 12 months following the study index date will be assessed for the diagnosed and undiagnosed CKD groups. Additionally, patients prescribed CKD treatments in absence of a code for hypertension and/or heart failure will be assessed. These analyses will help assess the clinical applicability of our methods to detect undiagnosed patients e.g., whether a significant proportion of patients without codes for CKD are being treated for the condition with medications indicated for other uses, e.g., HTN, HF.

- *Quality indicators*

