## **5.5 Sample Size and Power Calculations**

If the prevalence of undiagnosed CKD is between 60% and 80%, then a sample size of 1,000 patients will be sufficient to estimate the prevalence rate with a margin of error of  $\pm 3\%$  in a 95% CI per institution/country (6% width of 95% CI).

According to phase I of REVEAL-CKD in China: in the feasibility assessment report the Prevalence and consequences of undiagnosed chronic kidney disease in China, the number of patients who met the inclusion and exclusion criteria in the Chinese Renal Disease Data System (CRDS) database is about 27,000 and the number of patients who met the inclusion and exclusion criteria of sensitivity analysis in the CRDS database is about 46,000^3.

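### The logistic model for predictors of undiagnosed CKD leaves out index year, record length and hospital, although comorbidities and CKD codes both accumulate over an open-ended lookback, so comorbidity odds ratios can be biased towards looking protective

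*Protocol*

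**What the plan says.** Protocol section 2 sets the aim: "The overall aim of this study is to describe the prevalence and predictors of undiagnosed stage 3 CKD in priority countries". The predictors come from one model in section 5.2 (secondary objectives, diagnosed versus undiagnosed CKD): "A logistic regression model examining baseline factors associated with undiagnosed CKD will be conducted". Its covariates are named by reference: the section 4.3 characteristics "will be included in the model. Parameter estimates along with odds ratios, 95% C.I.s and p-values will be reported".

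Section 4.3 lists demographics, laboratory values, medications, comorbidities and the number of clinic visits in the year before index. Index year, length of record and hospital are not on the list.

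The time windows are:
- **Comorbidities (section 4.3):** "medical history/comorbidity will be assessed using all available data prior to the index date". Laboratory values and medications use a 12-month window instead.
- **CKD codes, the outcome (section 4.2):** a lookback of 12 months or more before the first eGFR, running to 6 months after index. Inclusion criterion 2 (section 3.4) sets the same minimum and no maximum.
- **Database (section 3.2):** CRDS is described "with data collected from 1994 to 2022", with an observation period of 1 January 2015 to 31 December 2020. Twenty hospitals are pooled.

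For time to diagnosis, section 5.2 says that, if possible, "association between baseline characteristics and time to CKD diagnosis will be assessed using relevant regression models". It fixes no covariates there.

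**The concern.** The predictor and the outcome are both the presence or absence of a code in the same patient's record, and both windows lengthen with that record. If record length differs between patients and is not in the model, two unrelated codes become associated because each had longer to appear. The direction is known: more record means more comorbidity codes and fewer patients without a CKD code, so the odds ratio for being undiagnosed falls below 1.

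Index year affects how much record is available. Hospital matters for another reason: the outcome is the absence of a code, so local coding habit acts on it directly. A covariate that is commoner in low-coding hospitals then acquires an odds ratio of its own.

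The model reports p-values on about 27,000 patients, so a modest artefact could be published as a significant predictor. The comorbidity subgroup prevalences (sections 4.4 and 5.2) share the record-length problem.

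**Working it through.** **1. The plan's own figure.** Section 5.5: "If the prevalence of undiagnosed CKD is between 60% and 80%, then a sample size of 1,000 patients will be sufficient" for a margin of ±3%. The half-width is 1.96 × √(p(1−p)/1,000), which is 3.04% at p = 0.60 and 2.48% at p = 0.80. The statement reproduces. It concerns prevalence only; no figure is given for the logistic model.

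**2. Spread of record length.** The minimum before index is 12 months plus more than 90 days between eGFRs, about 1.25 years. The maximum is about 6 years if lookback starts on 1 January 2015, and up to about 26 years (1994 to 2020) if all earlier data are used. The protocol does not give the distribution.

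**3. Expected crude odds ratio with no true association.** Let L be the record length, uniform over a range. Codes are independent given L:
- P(comorbidity recorded) = p × (1 − exp(−a·L)), with carriers p = 40–80% and a = 0.2–0.5 per year
- P(undiagnosed) = exp(−b·(L + 1)), with b = 0.06–0.10 per year

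All rates are assumptions. Example with p = 0.8, a = 0.5, b = 0.10:
- At L = 1: comorbidity 0.8 × 0.393 = 31%, undiagnosed exp(−0.2) = 82%
- At L = 5: comorbidity 0.8 × 0.918 = 73%, undiagnosed exp(−0.6) = 55%
- Averaged over L = 1–5: undiagnosed 66.0% with the comorbidity and 69.7% without
- OR = (0.660/0.340) / (0.697/0.303) = 0.84

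| Assumption | Spurious OR |
|---|---|
| Slow comorbidity coding, records 1–5 years | 0.84–0.91 (1.5–3.7 points) |
| Slow comorbidity coding, records 1–10 years | 0.71–0.89 (2.6–8.5 points) |
| Comorbidity coded at 2 per year, 50% carriers, records 1.25–6 or 1.25–12 years, 70% undiagnosed | 0.99 |
| CKD code possible only from 2 years before index to 6 months after, otherwise as the row above, comorbidity coded at 0.2–2 per year | 0.98–1.00 |

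Fast coding is not quite harmless everywhere: at 2 per year with 80% carriers, the formula above gives 0.96–0.97.

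**4. Chance range.** With n = 27,000, covariate prevalence 35% and 70% undiagnosed, SE(log OR) = √[Σ 1/(n·cell)] = 0.028, so 95% of null odds ratios lie in 0.95–1.06. The slow-coding results fall outside this range and the favourable ones inside it.

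**5. Does adjustment remove it?** Simulated logistic models: 27,000 patients, 20 hospitals, true OR 1, constant code rates, 70% undiagnosed, 50% with the comorbidity, age and visit count always included, records 1.25–6 years.

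| Scenario | Neither term | + record length | + record length and hospital |
|---|---|---|---|
| No hospital variation | 0.80 | 1.00 | 1.00 |
| Hospital coding varies (log-SD 0.5, correlation 0.5) | 0.68 | 0.82 | 0.99 |

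**6. Hospital alone.** Half the patients are in hospitals with 60% undiagnosed and half in hospitals with 80%. A null covariate is present in 30% and 50% respectively. Pooled OR = (0.29 × 0.19) / (0.11 × 0.41) = 1.22. With 65% and 75% undiagnosed it is 1.10. These inputs are hypothetical.

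**The case against.** **It is SAP detail.** Section 6.1 says an SAP will follow, and section 5.2 does not say that only section 4.3 variables enter. That is fair: adding terms contradicts nothing. But the protocol does name the covariate set, and following it as written leaves the terms out. That makes it a choice to improve rather than a detail left open.

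**The size depends on chosen rates.** This stands. A reader might infer that comorbidities must emerge as predictors by construction. The documents do not support that: with fast comorbidity coding, or CKD codes confined to the period near index, almost nothing is left. The longest-record scenarios also assume pre-2015 lookback, which the protocol does not settle.

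**The model is multivariable.** Age, visit count and other comorbidities may absorb part of the bias. With 12 mutually adjusted comorbidities, slow coding still gave about 0.85–0.91, so this helps only modestly. Visit count covers one year and does not measure record length.

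**Time to diagnosis.** A reader might infer that the same artefact affects that regression. It does not. Cohort 2 has no CKD code at index and its outcome accrues only afterwards, so one record length does not fill both sides. Only possible confounding by hospital and index year remains.

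**Hospital changes the question.** Correct. A descriptive study may legitimately report pooled associations; a hospital term gives within-hospital ones. Section 5.3.3 already cautions about coding accuracy and confounding across settings, but does not mention unequal lookback.

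**Conclusion.** The point holds for the logistic model and the comorbidity subgroup prevalences. Two open-ended windows that lengthen together, with no term for record length or index year, can bias comorbidity odds ratios for being undiagnosed below 1. The direction follows from the definitions, provided record length varies. The size does not follow: depending on assumed coding rates, the spurious crude odds ratio runs from about 0.71–0.91 to about 0.98–1.00.

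Hospital is a separate and more hypothetical source of confounding, suited to a supportive model. Medications and laboratory values, read over 12 months, do not have the growing-window problem. The overall prevalence and the Kaplan-Meier median are not challenged, and the sample-size statement is unaffected.

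**What to change.** 1. In the section 5.2 logistic model, add index year (categorical) and length of available record before index (spline or categories), defined for example as time from first recorded encounter to index.
2. Report a supportive version with hospital as a fixed effect or stratum, read as within-hospital associations.
3. As a further supportive analysis, repeat the model and the comorbidity subgroup prevalences with one fixed lookback for comorbidities and CKD codes. The 12 months before index would be available for every patient meeting inclusion criterion 2. Anchoring at the first eGFR would leave the interval between eGFRs, up to 730 days, varying. The CKD-code window would still close 6 months after index.
4. State whether pre-2015 data are used for lookback, and tabulate record length by diagnosis status.
5. In the time-to-diagnosis regression, consider hospital and index year as confounders.

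The cost is SAP wording and a few terms from data already held. With hospital this is about 25–30 degrees of freedom (19 for hospital, at most 5 for year, the rest for record length) out of about 27,000 patients. The fixed-window run loses some sensitivity, because patients with only an older CKD code count as undiagnosed, so its prevalence should not replace the primary estimate.

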#### 4.3.1 Baseline Patient Characteristics and Comorbidities

The following baseline characteristics will be assessed:

- *Demographic variables*
  - Age in years at index date, continuous and categorical (<45, 45-<65, 65-<75, ≥75 years)
  - Sex, categorical (female, male, not available)
  - Ethnicity (or education if available) categorical
  - Family history of CKD
  - Smoking status
  
- *Physiological/laboratory values*
  - Height (cm), continuous
  - Weight (kg), continuous
  - Body mass index (BMI), continuous, calculated as  $\text{kg/m}^2$  where  $kg$  is weight and  $m$  is height
  - Hemoglobin (Hb), g/dL
    - Hb >12
    - Hb 10-12
    - Hb 8-10
    - Hb <8
  - Hematocrit
    - <40%
  - eGFR (mL/min/1.73m^2) using CKD-EPI or MDRD equation, continuous
  - Potassium, highest and closest to index date within 1 year prior to index, mmol/l
    - 5.5–5.9 (mild hyperkalemia)
    - 6.0–6.4 (moderate hyperkalemia)
    - >6.5 (severe hyperkalemia)
  - Urine albumin creatinine ratio (UACR, mg/g), continuous, calculated as urine albumin (mg/dL) / urine creatinine (g/dL)
  - Serum uric acid levels, continuous
  - Total cholesterol, continuous
  - Low density lipoprotein (LDL) cholesterol, continuous

- High density lipoprotein (HDL) cholesterol, continuous
- Triglycerides, continuous
- Serum calcium, continuous
- Serum phosphate, continuous
- Serum bicarbonate, continuous
- Albuminuria, continuous
- Serum albumin, continuous
  
- *Medications*
  - Cardiovascular
    - ACE inhibitors
    - ARBs
    - Aldosterone receptor agonists (MRA)
    - Angiotensin receptor-neprilysin inhibitor (ARNI)
    - Loop diuretics
    - Beta blockers
    - Thiazide diuretics
    - Calcium channel blockers
    - Alpha blockers, e.g., clonidine and methyldopa
  - Glucose-lowering drugs
    - Metformin
    - Sulphonylurea
    - Dipeptidyl peptidase 4 inhibitors (DPP-4i)
    - Glucagon-like peptide-1 receptor agonist (GLP1-RA)
    - Insulin
    - Other oral anti-diabetes (OADs), (sulfonylureas, thiazolidinediones, biguanides, alpha-glucosidase inhibitors)
  - Lipid-lowering drugs
  - SGLT2 inhibitors
  - Antithrombotic/antiplatelet agents
  - Anticoagulants
  
- *Medical history/comorbidities*
  - Atherosclerotic cardiovascular disease (ASCVD)
    - Myocardial infarction (MI)
    - Unstable angina (UA)

- Stable angina
  - Coronary revascularization
  - Stroke (ischemic or hemorrhagic)
- Heart failure
- Atrial fibrillation
- Peripheral arterial disease (PAD)

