## **5. STATISTICAL ANALYSIS PLAN**

### **5.1 Statistical Methods – General Aspects**

This study is purely descriptive without any formal hypotheses. The main focus will be on quantifying the prevalence and consequences of undiagnosed CKD. Key assumptions include: our ability to define undiagnosed CKD subjects with only eGFR as an indicator of a future diagnosis of CKD by a physician, secondly, that absence of claims or health record data for CKD or other comorbid events indicate that the diagnosis of the condition never occurred, and finally, the timing of recorded CKD diagnosis in the database corresponds with the time when the first CKD diagnosis was made by the health care provider (assuming minimum lag in data recording).

Missing data for baseline measures will be assessed and addressed as a categorical variable with a level for missingness. All reported measures will be summarized in the study tables. Point estimates and their 95% C.I.s will be presented in the final analyses.

Data analysis will take place in a step-wise approach where the objectives pertinent to the describing the undiagnosed CKD patient cohort will be performed first and results will be reviewed by the study team before the analysis on the rest of the objectives take place.

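### The logistic model for undiagnosed CKD takes in an overlapping covariate list and gives no adjusted result on the prevalence scale that the study uses

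*Protocol*

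**What the plan says.** Section 2 gives the overall aim as describing the prevalence and the predictors of undiagnosed stage 3 CKD. The predictor part is carried by a logistic regression in section 5.2 (secondary objectives, diagnosed versus undiagnosed CKD). Its outcome is the absence of a CKD diagnosis, and section 5.2 directs that the section 4.3 characteristics go into the model. The output is fixed: "Parameter estimates along with odds ratios, 95% C.I.s and p-values will be reported".

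The section 4.3.1 list includes "Age in years at index date, continuous and categorical". It also has height, weight and BMI; diabetes followed by type 1, type 2 and unclassified; ASCVD followed by its component events; and metformin and sulphonylurea, followed by an 'other oral' class that names sulfonylureas and biguanides among its members.

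Section 5.1 states: "This study is purely descriptive without any formal hypotheses". Section 3.1 says the same, and section 5.3.2 marks multiplicity adjustment as not applicable. Section 5.5 plans on "If the prevalence of undiagnosed CKD is between 60% and 80%, then a sample size of 1,000 patients" and puts the eligible number "in the Chinese Renal Disease Data System (CRDS) database is about 27,000".

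Other results bear on the same question. The same part of section 5.2 plans absolute standardized differences between diagnosed and undiagnosed patients. The primary analysis stratifies undiagnosed prevalence by the section 4.4 subgroups. Section 5.1 promises 95% CIs.

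**The concern.** The sentence that sends section 4.3 into the model is an instruction, not a gap. The list was drawn up to describe patients, so it holds parent categories with their parts and derived quantities with their ingredients. That suits a baseline table. In a regression, each coefficient is conditional on all the others, and several of these terms then have no meaning of their own.

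The second matter is the scale of the answer. The primary objective and the trend analysis are expressed as prevalence, but the only adjusted predictor result is an odds ratio. For an outcome expected in most patients, an odds ratio is far from a prevalence ratio, and how far depends on the reference prevalence. A reader moving from the prevalence tables to the predictor table could misjudge the size of the associations. At stake is the usefulness of the predictor half of the aim. No primary estimate is affected.

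**Working it through.** **1. The plan's own figure.** Inputs from section 5.5: n = 1,000, prevalence p of 60-80%, margin ±3 points. Half-width = 1.96 × √[p(1−p)/n]:
- p = 0.60: 3.04 points
- p = 0.70: 2.84 points
- p = 0.80: 2.48 points

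The stated margin reproduces, with slight rounding at 60%.

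**2. The overlapping terms, if all entered.**
- *Age.* The categories are a function of continuous age. With both in the model, a category coefficient is a jump at a cut-point given a linear trend. Neither term alone is the age effect.
- *Height, weight, BMI.* BMI is computed from the other two, so none can vary while both others are held fixed.
- *Diabetes.* If the three types are mutually exclusive and cover every diabetic patient, diabetes = T1D + T2D + unclassified. That is an exact linear dependence, and the four coefficients cannot all be estimated.
- *ASCVD.* If it means any listed component, it equals the sum of the components in everyone with none or one. Its coefficient then rests only on patients with two or more.
- *Oral glucose-lowering drugs.* A metformin or sulphonylurea user also belongs to the 'other' class as listed, so the separate drug coefficients do not compare users with non-users.

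**3. Odds ratio against prevalence scale.** OR = [p1/(1−p1)] / [p0/(1−p0)]; prevalence ratio = p1/p0; difference = p1−p0.

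| p1 v p0 | Odds ratio | Prevalence ratio | Difference |
|---|---|---|---|
| 70% v 60% | 2.333/1.5 = 1.56 | 1.17 | 10 points |
| 80% v 70% | 4/2.333 = 1.71 | 1.14 | 10 points |
| 80% v 60% | 4/1.5 = 2.67 | 1.33 | 20 points |

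Conversely, one odds ratio of 2.0 stands for different things at different reference prevalences:
- 60%: ratio 1.25, difference 15.0 points
- 70%: ratio 1.18, difference 12.4 points
- 80%: ratio 1.11, difference 8.9 points

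**4. What p-values pick out at N = 27,000.** The protocol gives neither a threshold nor factor frequencies. I assume two-sided 0.05, a range of frequencies, and an unadjusted two-group comparison.

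The estimate that just reaches p = 0.05, for a factor held by half the patients at 70% undiagnosed, is OR = exp[1.96/√(27,000 × 0.21 × 0.25)] = exp(0.052) = 1.05. That is about 0.21 × 0.052 = 0.011, or 1.1 points.

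Power = Φ[(Δ − 1.96·SE0)/SE1], with SE0 pooled and SE1 unpooled. For the half-and-half factor and a reference prevalence of 60% to 80%, a true difference of 1 point has 39-55% power and one of 2 points has 92-99%. The difference needed for 80% power is:

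| Share of patients with the factor | Points (reference 80% to 60%) |
|---|---|
| 50% | 1.4-1.7 |
| 20% | 1.7-2.1 |
| 10% | 2.2-2.8 |
| 5% | 3.1-3.8 |
| 1% | 6.6-8.3 |

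In the multivariable model the detectable differences would usually be larger.

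**The case against.** **The odds ratio is legitimate.** A reader might infer that the plan makes associations look far larger than they are. The documents do not support that. An odds ratio is not biased by a common outcome, and the protocol nowhere says it will be read as a prevalence ratio. The 60-80% range is also a conditional sample-size assumption, not an observed rate. This stands, so the choice of odds ratio is not an error.

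**Almost everything will be significant.** A reader might infer this from the sample size. It fails: a 1-point difference has at most 55% power even in the most favourable case, and a factor held by 1% of patients needs 6.6-8.3 points for 80% power. With no threshold and no hypothesis, marking multiplicity as not applicable is consistent, and a count of expected false positives has nothing in the plan to attach to.

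**Other results show effect size.** The standardized differences do not depend on sample size, and the subgroup prevalences are on the right scale. Both count. But the first compare covariate distributions between outcome groups, not prevalence across factor levels. The second are unadjusted and limited to the section 4.4 list. Neither is an adjusted prevalence result.

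**Coding belongs in the SAP.** Section 6.1 says one will be written, and no analyst is likely to enter two age codings knowingly. This has force and limits the weight of the point. Still, the protocol does not stay silent: it directs the section 4.3 list into the model, so a SAP that follows it inherits the problem.

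**One coding per construct does not settle everything.** Diabetic nephropathy and hypertensive kidney failure are listed covariates, and related codes count as a CKD diagnosis in Table A1. The protocol gives no code list for covariates, so whether they coincide cannot be decided here and is not part of this point.

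**Conclusion.** The point holds as a correctable weakness in a secondary analysis. The covariate instruction, taken as written, yields terms that are redundant or not separately interpretable. For diabetes with its types it yields terms that are not estimable, if the types are exclusive and exhaustive. Separately, the model gives no adjusted result on the prevalence scale. At the planning prevalence of 60-80%, the gap between the scales is material for anyone who reads one as the other: 2.67 against 1.33 for a 20-point difference, 1.71 against 1.14 for a 10-point difference.

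On p-values, the supportable statement is limited: at about 27,000 patients they flag differences of roughly 1-2 points for common factors, but not for rare ones. This rests on the assumed 0.05 level, the assumed factor frequencies and the unadjusted approximation. A reader might go further and conclude that odds ratios should be demoted or p-values removed. That is a preference about presentation, and the documents do not make it necessary.

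**What to change.** In section 5.2, replace the direction to include the section 4.3 characteristics with a model list that has one coding per construct:
- age once;
- BMI without height and weight;
- diabetes type without the parent term;
- either ASCVD or its components;
- drug classes that do not overlap.

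Section 4.3 can stay as it is for the descriptive tables.

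From the same logistic fit, add the model-standardised prevalence of undiagnosed CKD at each level of each factor, with adjusted prevalence differences or ratios and 95% CIs, alongside the odds ratios. Label any p-values descriptive, in line with sections 3.1 and 5.1.

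The cost is a wording change, a small post-estimation step and extra table columns. No new data are needed.

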### 3. Use of recommended medications

- Statin prescription within one year
- ACEis or ARBs within one year
- SGLT2 in patients with diabetes
- SGLT2 in patients without diabetes

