## **5.3 Bias**

### **5.3.1 Methods to Minimize Bias**

The identification of patients with undiagnosed vs. diagnosed CKD relies on laboratory eGFR results, and the assumption that the absence of a CKD diagnosis code (e.g., ICD 9/10)

indicates that the patient is yet to be diagnosed with the condition by the physician. As this information is being inferred from EMR records, our assumptions may result in the misclassification of patients. The accuracy of our algorithm to identify patients with undiagnosed CKD is unknown. However, bias due to misclassification should be minimized, as our definition of CKD using eGFR results is based on an established clinical definition. Additionally, for patients identified as “undiagnosed”, we will also examine whether therapies for CKD (e.g., ACEi, ARB) are administered in the 12 month period following the index date (2nd eGFR result between 30-<60) to understand the likelihood that the patient is actually undiagnosed e.g., a code for CKD does not appear in their medical records but they are receiving treatment for CKD.

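### The check for hidden CKD treatment counts SGLT2i but does not screen for diabetes, and its "and/or" wording leaves the hypertension and heart-failure screen open to two readings

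*Protocol*

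**What the plan says.** Protocol section 5.2, under the secondary objective comparing diagnosed and undiagnosed CKD, sets up a treatment check in three steps.

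- It defines the treatments and the window: "The proportions of patients receiving treatment for CKD (ACEi, ARB and SGLT2i) within 12 months following the study index date will be assessed" in the diagnosed and undiagnosed groups.
- It adds a screen for other indications: "patients prescribed CKD treatments in absence of a code for hypertension and/or heart failure will be assessed".
- It gives the purpose, which is to learn "whether a significant proportion of patients without codes for CKD are being treated for the condition with medications indicated for other uses, e.g., HTN, HF".

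Section 5.3.1 (Methods to Minimize Bias) refers to the same idea for patients classed as undiagnosed: "we will also examine whether therapies for CKD (e.g., ACEi, ARB) are administered in the 12 month period following the index date", in order "to understand the likelihood that the patient is actually undiagnosed".

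Elsewhere the protocol treats diabetes as relevant to SGLT2i use. Domain 3 of the quality indicators in section 4.2 has one line for "SGLT2 in patients with diabetes" and another for patients without diabetes. Section 4.3.1 lists type 1, type 2 and unclassified diabetes among the recorded comorbidities. Section 4.3 states that "medication use will be ascertained on or within 12 months before the index date".

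**The concern.** The check can only inform the reader if a prescription that passes the screen is hard to explain by anything other than CKD. For SGLT2i the screen leaves out diabetes, the one condition by which the protocol itself divides their use. Prescriptions with an ordinary alternative explanation would then be shown as a sign that an uncoded patient is really being treated for CKD.

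The wording of the screen adds a second problem. It can require that both codes are absent, or only that at least one is. Under the second reading, an ACEi user with coded hypertension and no heart failure code still passes, which defeats the purpose for the commonest alternative explanation that the protocol names.

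At stake is the interpretation of the undiagnosed group. Section 5.3.1 says that the accuracy of the algorithm is unknown. The first two sensitivity analyses vary the code lists and the third varies an entry criterion, so this check is the one that brings in evidence other than diagnosis codes. An inflated result would suggest that more of the undiagnosed patients are known to their physicians than is the case.

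**Working it through.** The protocol states no figure for this check, so there is none to reproduce. The texts are compared first; two illustrations follow.

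**1. Who passes the screen**

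| Uncoded patient (no CKD code) | Drug | Screen in section 5.2 as worded | Alternative explanation recorded in the protocol's data |
|---|---|---|---|
| Diabetes, no hypertension or heart failure code | SGLT2i | Passes | Diabetes |
| Hypertension code, no heart failure code | ACEi or ARB | Passes if one missing code is enough; removed if both must be missing | Hypertension |
| None of the three codes | Any of the three | Passes | None of the three |

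Two groups of patients with diabetes do not add to the problem. Those with a hypertension or heart failure code are removed if both codes must be absent. Those coded as diabetes with renal manifestation already count as diagnosed, because Table A1 includes these codes in the primary definition.

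**2. How large the diabetes effect could be (assumed inputs)**

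The protocol gives no diabetes or SGLT2i rates. Among undiagnosed patients without a hypertension or heart failure code, let d be the share with diabetes, u the share of these taking an SGLT2i for diabetes, and h the true share with hidden CKD treatment, taken as independent.

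Apparent share = 1 − (1 − h)(1 − d·u). Spurious part = (apparent − h) / apparent.

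| d | u | h | Apparent share | Spurious part |
|---|---|---|---|---|
| 10% | 2% | 10% | 1 − 0.90 × 0.998 = 10.18% | 0.18 / 10.18 = 2% |
| 20% | 5% | 5% | 1 − 0.95 × 0.99 = 5.95% | 0.95 / 5.95 = 16% |
| 40% | 15% | 2% | 1 − 0.98 × 0.94 = 7.88% | 5.88 / 7.88 = 75% |

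The first and last rows are the extremes over d = 10–40%, u = 2–15% and h = 2–10%. The check could be almost intact or mostly spurious, and its output would not show which.

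**3. How much the conjunction matters (assumed inputs)**

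Let a be the share with a hypertension code and b the share with a heart failure code.

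- Neither code present, if independent: (1 − a)(1 − b).
- At least one code absent: 1 − a·b.
- The gap is the share with exactly one of the two codes.

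With a = 60% and b = 15% (assumed), the first is 0.40 × 0.85 = 34% and the second is 1 − 0.60 × 0.15 = 91%. The gap of 57 percentage points equals 0.60 × 0.85 + 0.15 × 0.40 = 0.51 + 0.06. The two readings therefore describe very different populations.

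**The case against.** Several counter-arguments have force.

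- The purpose sentence in section 5.2 gives hypertension and heart failure only as examples, and section 6.1 leaves procedures to a later SAP. This is fair, but the sentence that states the screen names just those two conditions. An SAP that follows it literally would carry the omission forward.
- Section 5.3.1 names only ACEi and ARB as examples of therapy, and section 4.3.1 lists SGLT2 inhibitors apart from the glucose-lowering drugs. Section 5.2, however, names SGLT2i outright as CKD treatment, and section 4.2 splits its use by diabetes.
- Some SGLT2i users with diabetes may be treated for CKD, so not every such patient is wrongly flagged. This stands, and it makes the illustration above an upper reading for given d and u.
- Continued use of a drug is also evidence that a patient is being treated. This stands too, so separating new starts is an option and not a correction.

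A reader might go further and infer that the 12-month treatment window is faulty because diagnosis status is settled only at 6 months after index. The documents do not support this for the hidden-treatment check: undiagnosed patients have no CKD code through month 6 by definition, so treatment in those months is exactly the uncoded treatment being sought.

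A reader might also infer two conflicting one-year figures, one in section 5.2 and one in the quality indicators. Section 4.2 attaches one year to statins and to ACEi or ARB, and gives no window for SGLT2i. For ACEi and ARB the two analyses serve different purposes, so different windows are not a contradiction. Starting the group comparison at month 6 would largely repeat the planned ACEi/ARB indicator.

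**Conclusion.** The point holds for the indication screen. As worded, section 5.2 lets SGLT2i use in patients with diabetes stand as possible hidden CKD treatment, and it does not settle whether one or both of the hypertension and heart failure codes must be absent.

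The consequence is limited. The check is supportive and descriptive, it reclassifies no patient, and the primary prevalence of undiagnosed stage 3 CKD is the same with or without it. It would be wrong to infer a bias in the primary estimate.

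The size cannot be derived from the protocol. The range of about 2% to 75% rests wholly on assumed rates, on independence, and on treating the SGLT2i use in question as use for diabetes alone. It shows only that the omission may be trivial or may dominate the result.

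**What to change.** Reword the screen in section 5.2 by drug class:

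- **SGLT2i:** count patients with no code for hypertension, heart failure or diabetes; or report the result separately with and without diabetes, as the quality indicators in section 4.2 already do.
- **ACEi and ARB:** count patients with neither a hypertension code nor a heart failure code, and drop the ambiguous conjunction.
- **Optional:** report new starts separately from continued use, with the 12-month baseline medication data described in section 4.3.

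All the variables are already listed, so the cost is wording and one extra filter. The price is fewer patients in the check. Excluding diabetes also loses any SGLT2i users with diabetes who are in fact treated for CKD; reporting by diabetes status keeps them visible. The 12-month window needs no change on this account.
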